#### 11.4.1 Premature termination of the study

The study can be prematurely terminated on the advice of the Data Safety Monitoring Board if safety concerns are detected at any time during the study.

The study may also be prematurely terminated in case of overwhelming evidence of efficacy or futility, defined as highly statistically significant difference (i.e.  $P < 0.001$ ) in the primary outcome or a highly statistically significant difference in the important secondary outcome death before hospital discharge, from interim analysis. Interim analysis for efficacy or futility will be carried out after approximately 50% of participants have completed the study (i.e. after the completion of 126 patients) using the Haybittle- Peto stopping boundary.

#### 11.5 Discontinuation/withdrawal of subjects from study protocol

Subjects have the right to voluntarily discontinue study treatment or withdraw from the study at any time for any reason without any consequences. Subjects will be withdrawn from the study for any of the following reasons:

- withdrawal of consent by the subjects' parent(s)/guardian(s)
- ineligibility (either arising during the study or retrospectively having been overlooked at screening)
- lost to follow-up

As data is collected on enrolled infants during their hospital stay, we anticipate minimal loss to follow-up. In the event of transfer of a patient to a regional centre following discharge from the tertiary unit, we will ensure 3 documented attempts are made to contact any subject lost to follow-up. Parents have the right to withdraw consent for participation in the study at any stage and this will not affect their infant's access to the best available treatment and care at the birth hospital or other hospital to which they might have been referred.

All subjects who discontinue should comply with protocol specified follow-up procedures. The only exception to this requirement is when a subject withdraws consent for all study procedures.

If a subject is withdrawn before completing the study, the reason for withdrawal must be entered on the appropriate case report form (CRF) page.

If a subject is withdrawn due to an adverse event, the investigator will arrange for follow-up visits until the adverse event has resolved or stabilised.

## 12 TREATMENT OF TRIAL SUBJECTS

### 12.1 Description of study treatment(s)

Surfactant (Curosurf, Chiesi Farmaceutici, Parma, Italy) is a white suspension. Each mL of suspension contains 80mg poractant alfa (surfactant extract) that includes 76mg of phospholipids and 1mg of protein of which 0.45mg is SP-B and 0.59mg is SP-C.

There are two vials of Curosurf: 1.5ml vial (contains 120mg poractant alfa) or 3ml vial (240mg poractant alfa).

The 120mg vial will be given to infants <26 weeks gestation and a full 240mg vial to infants 26-28 weeks gestation.

The surfactant will be warmed by the clinicians prior to being drawn up in a sterile syringe as per manufacturer's recommendation. This will be done by opening the mouth gently and injecting the surfactant as a single bolus into the oropharynx using a syringe without a needle attached. This will be done as soon as possible after delivery, ideally before the umbilical cord has been clamped.

The dosing recommendations for initial treatment with Curosurf when given by endotracheal tube are:

- 200mg/kg for established RDS
- 100 – 200mg/kg for prophylaxis

One or two further doses of 100mg/kg Curosurf may be given to infants who have persistent respiratory distress despite treatment with surfactant (maximum recommended dose 400mg/kg).

Infants in our study will not be weighed prior to enrolment. The 50th centile for birth weight (BW) for boys and girls according to gestational age (GA) is shown below

| GA (weeks) | Girls BW (kg) | Boys BW (kg) |
|------------|---------------|--------------|
| 23         | 0.550         | 0.600        |
| 24         | 0.650         | 0.700        |
| 25         | 0.775         | 0.800        |
| 26         | 0.850         | 0.900        |
| 27         | 0.975         | 1.050        |

|    |       |       |
|----|-------|-------|
| 28 | 1.100 | 1.150 |
|----|-------|-------|

In our study, infants <26 weeks will receive a full 120mg vial of Curosurf. We estimate that this will provide dosing in the therapeutic range as indicated below:

| GA (weeks) | G r s BW (kg) | Dose (mg/kg) | Boys BW (kg) | Dose (mg/kg) |
|------------|---------------|--------------|--------------|--------------|
| 23         | 0.550         | 218          | 0.600        | 200          |
| 24         | 0.650         | 185          | 0.700        | 171          |
| 25         | 0.775         | 155          | 0.800        | 150          |

In our study, infants 26–28 weeks will receive a full 240mg vial of Curosurf. We estimate that this will provide dosing in the therapeutic range as indicated below:

| GA (weeks) | G r s BW (kg) | Dose (mg/kg) | Boys BW (kg) | Dose (mg/kg) |
|------------|---------------|--------------|--------------|--------------|
| 26         | 0.850         | 282          | 0.900        | 267          |
| 27         | 0.975         | 246          | 1.050        | 229          |
| 28         | 1.100         | 218          | 1.150        | 209          |

## 12.2 Formulation, packaging and handling

CUROSURF (poractant alfa), manufactured by and licensed from Chiesi Farmaceutici, S.p.A., Parma, Italy, 43100.

The suspension is available in sterile, rubber-stoppered clear glass vials containing:

1.5ml (120mg poractant alfa (surfactant extract)) of suspension: NDC Number 10122-510-01

3ml (240mg poractant alfa (surfactant extract)) of suspension: NDC Number 10122-510-03

The CUROSURF used for the trial (for all sites except Swedish sites) will be contained in individual ziplock bags and will have a sticker label on it containing the required clinical trial label. CUROSURF will be labelled in line with the recommendations in Annex 13 of the European Directive on Good Manufacturing Practice in clinical trials conducted with marketed investigational products.

Specifically, for sites conducting the trial in Sweden only, the Curosurf used in the trial will be the same as used routinely in the NICU. The Curosurf will be prescribed as per clinical routine and is only administered by appropriate health personnel. Due to the nature of the IMP handling, the Curosurf used in the study will have the commercial label but no study specific label, in line with LVFS 2011:19.

## 12.3 Storage and disposition of study treatment(s)

The suspension is stored in a refrigerator at +2 to +8 degrees Celsius, protected from light. Vials are for single use only. After opening the vial the unused portion is discarded.

The refrigerator temperature must be recorded on a temperature log on a daily basis to record proper function.

Curosurf is used routinely in the NICU via endotracheal administration. The suspension of Curosurf for use in this study is no different than that used routinely. However rather than administering the medication endotracheally, it will be given via the oropharynx. Due to the emergent nature of some of these deliveries, the Curosurf used will be stored in the refrigerator in the NICU as per routine practice however will be separate for specific use for the POPART study (labelling on the IMP for all sites except Swedish sites). The study treatment will be stored and locked in a secure place until they are dispensed for use and the supply used for the trial will only be used within the context of this study.

## 12.4 Accountability of the study treatment

The study medication will be supplied by Chiesi Farmaceutici. The investigator is responsible for the control of the treatment(s) under investigation. Adequate records for the receipt and disposition of the IMP must be maintained.

The investigator will use a standard prescription form and the investigator/research nurse will collect the medication from the pharmacy as per routine practice in the country.

In our study, the intervention of OROPHARYNGEAL SURFACTANT is given as a once-off dose at birth. Accountability and compliance with study treatments will be assessed by maintaining dispensing and return records.

### 12.5 Assessment of compliance

Compliance with study medications will be assessed through documentation at delivery in clinical notes and the study medications packaging will be stored post administration.

The investigator is responsible for ensuring that the study treatment is administered in compliance with the protocol. The intervention of 'OROPHARYNGEAL SURFACTANT' is given as a once-off dose at birth, thus compliance at later dates is not an issue.

### 12.6 Overdose of study treatment

The overdose of a study treatment will be handled in the same way as would any overdose of a medication. There have been no reports of over-dosage following the administration of Curosurf.

### 12.7 Prior and concomitant therapy

Any medication, other than the study medication taken during the study will be recorded in the CRF.

All participants will be newly-born infants, and so will not have any prior therapies.

We will record medication other than the study medication taken during the study in the CRF as follows:

- Postnatal corticosteroids for ventilator dependence
- Medical treatment for a patent ductus arteriosus
- Medical management of Necrotising enterocolitis ( $\geq$  Bell's stage 2)
- Intravitreal injection for retinopathy of prematurity

#### 12.7.1 Permitted medications/non-investigational medicinal products

The only medications which will be used during the study are those medications that are routinely used on preterm babies in NICU.

#### 12.7.2 Prohibited medications

There are no contraindicated medications for use in this study.

## 13 SAFETY REPORTING

Adverse events (AEs) will be recorded throughout the study and will be evaluated and classed according to the definitions below (European Directive 2001/20/EC). All adverse events will be collected and recorded in accordance with the detailed guidance on the collection, verification and presentation of adverse event/reaction reports arising from clinical trials on medicinal products for human use ('CT-3') while referencing the protocol specific guidance included in Section 13.3.

### 13.1 Definitions

#### 13.1.1 Adverse event (AE)

Any untoward medical occurrence in a patient or clinical trial subject administered a medicinal product and which does not necessarily have a causal relationship with this treatment.

An adverse event can therefore be any unfavourable and unintended sign (including an abnormal laboratory finding, for example), symptom or disease temporally associated with the use of a medicinal product, whether or not considered related to the medicinal product

#### 13.1.2 Adverse reaction (AR)

All untoward and unintended responses to a medicinal product related to any dose.

The phrase 'responses to a medicinal product' means that a causal relationship between a study medication and an AE is at least a reasonable possibility, i.e., the relationship cannot be ruled out.

All cases judged by either the reporting medically qualified professional or the sponsor as having a reasonable suspected causal relationship to the study medication qualify as adverse reactions.

### 13.1.3 Serious adverse event

Any untoward medical occurrence or affect that at any dose:

- results in death,
- is life-threatening\*,
- requires hospitalisation or prolongation of existing hospitalisation,
- results in persistent or significant disability or incapacity,
- is a congenital anomaly or birth defect
- important medical events\*\*

\*Regarding a life-threatening event, this refers to an event in which the subject was at risk of death at the time of the event; it does not refer to an event which hypothetically might have caused death if it were more severe.

\*\*Some medical events may jeopardise the subject or may require an intervention to prevent one of the above characteristics/consequences. Such events (hereinafter referred to as 'important medical events') should also be considered as 'serious' in accordance with the definition

### 13.1.4 Severe adverse events

The term 'severity' is used here to describe the intensity of a specific event. This has to be distinguished from the term 'serious'.

### 13.1.5 Suspected unexpected serious adverse reactions

An adverse reaction, the nature or severity of which is not consistent with the applicable product information (e.g. investigator's brochure for an unauthorised investigational medicinal product or summary of product characteristics for an authorised medicinal product).

## 13.2 Evaluation of AEs and SAEs

Seriousness, causality, severity and expectedness should be evaluated.

### 13.2.1 Assessment of seriousness

The investigator should make an assessment of seriousness as defined in section 13.1.

### 13.2.2 Assessment of causality

All adverse events judged by either the investigator or the sponsor as having a reasonable suspected causal relationship to an investigational medicinal product qualify as adverse reactions.

The causality assessment given by the investigator should not be downgraded by the sponsor.

The investigator/sponsor must make an assessment of whether the AE/SAE is likely to be related to treatment according to the following definitions:

#### Unrelated

Where an event is not considered to be related to the study medication.

#### Possibly

Although a relationship to the study medication cannot be completely ruled out, the nature of the event, the underlying disease, concomitant medication or temporal relationship make other explanations possible.

#### Probably

The temporal relationship and absence of a more likely explanation suggest the event could be related to the study medication.

All AEs/SAEs judged as having a reasonable suspected causal relationship (e.g. possibly, probably) to the study medication will be considered as ARs/SARs.

All AEs/SAEs judged as being related (e.g. possibly, probably) to an interaction between the study medication and another medication will also be considered to be ARs/SAR.

Alternative causes such as natural history of the underlying disease, concomitant therapy, other risk factors and the temporal relationship of the event to the treatment should be considered.

### 13.2.3 Assessment of severity

The investigator will make an assessment of severity for each AE/SAE and record this on the CRF according to one of the following categories:

#### Mild

An event that is easily tolerated by the subject, causing minimal discomfort and not interfering with everyday activities.

#### Moderate

An event that is sufficiently discomforting to interfere with normal everyday activities.

#### Severe

An event that prevents normal everyday activities.

Note: the term 'severe', should not be confused with 'serious' which is a regulatory definition based on subject/event outcome or action criteria

### 13.2.4 Assessment of expectedness

The expectedness of an adverse reaction will be determined by the sponsor according to the reference document e.g. the investigator's brochure for a non-authorised investigational medicinal product, or the summary of product characteristics for an authorised medicinal product which is used according to the terms and conditions of the marketing authorisation. For CUROSURF the summary of product characteristics will be used as the reference safety information for assessment of expectedness of an adverse reaction.

## 13.3 Reporting procedures for all adverse events

The investigational medicinal product (IMP), Curosurf, is licensed for use for prevention and treatment of respiratory distress syndrome (RDS) in premature infants in Europe for more than 25 years. It is given as a single dose by the endotracheal route and may on occasion be repeated. It has an excellent safety profile.

Many of the adverse events which are listed in the Summary of Product Characteristics for Curosurf (portactant alfa) below occur commonly in preterm infants who are admitted to the Neonatal Intensive Care Unit (NICU), whether or not they have received surfactant. Others are seen infrequently in this population, whether or not they have received surfactant.

| System organ Class                              | Adverse Reaction                     | Frequency |
|-------------------------------------------------|--------------------------------------|-----------|
| Infections and infestations                     | Sepsis                               | Uncommon  |
| Nervous system disorders                        | Haemorrhage intracranial             | Uncommon  |
| Cardiac disorders                               | Bradycardia                          | Rare      |
| Vascular disorders                              | Hypotension                          | Rare      |
| Respiratory, thoracic and mediastinal disorders | Bronchopulmonary dysplasia           | Rare      |
|                                                 | Pneumothorax                         | Uncommon  |
|                                                 | Pulmonary haemorrhage                | Rare      |
|                                                 | Hyperoxia                            | Not known |
|                                                 | Cyanosis neonatal                    | Not known |
| Investigations                                  | Apnoea                               | Not known |
|                                                 | Oxygen saturation decreased          | Rare      |
|                                                 | Electroencephalogram abnormal        | Not known |
| Injury, poisoning and procedural complications  | Endotracheal intubation complication | Not known |

AEs that are directly related to the underlying condition of extreme prematurity do not need to be reported as an AE on this study, for example:

1. Bradycardia, hypotension, hyperoxia, cyanosis, apnoea, oxygen desaturations  
These events frequently occur several times per day in this population, whether or not they have received surfactant. Most often these events are short in duration and not of clinical significance. Regular reporting of these adverse events in the CRF is not required.
2. Intracranial haemorrhage  
Some degree of intracranial haemorrhage is detected in  $\geq 30\%$  of infants in this population, whether or not they have received surfactant. Regular reporting of these adverse events in the CRF is not required. All enrolled infants are being screened for intracranial haemorrhage; it is being recorded in the CRF and measured as a secondary outcome.
3. Bronchopulmonary dysplasia  
Bronchopulmonary dysplasia occurs in up to  $\geq 50\%$  in this population of infants, whether or not they have received surfactant. Regular reporting of these adverse events in the CRF is not required. All enrolled infants are being screened for bronchopulmonary dysplasia; it is being recorded in the CRF and measured as a secondary outcome.
4. Pneumothorax, pulmonary haemorrhage  
These are rare events in this population of infants, whether or not they have received surfactant. Regular reporting of these adverse events in the CRF is not required. All enrolled infants are being screened for pneumothorax and pulmonary haemorrhage; it is being recorded in the CRF and measured as a secondary outcome.
5. Endotracheal intubation complication  
Endotracheal intubation complication is not relevant as we are not giving surfactant via this route of administration as the intervention arm for this study. Regular reporting of these adverse events in the CRF is not required.

Only AEs which are not directly associated to the underlying condition of extreme prematurity should be reported. The following information will be recorded: description, date of onset and end date, severity, assessment of relatedness to the study medication, other suspect medication or device and action taken. Follow-up information should be provided as necessary.

AEs considered related to the study medication as judged by an investigator or the sponsor will be followed until resolution or until the event is considered stable. All related AEs that result in a subject's withdrawal from the study or are present at the end of the study, should be followed up until a satisfactory resolution occurs.

It will be left to the investigator's clinical judgment whether or not an AE is of sufficient severity to require the subject's removal from the study. If this occurs, the subject must undergo an end-of-study assessment and be given appropriate care under medical supervision until symptoms cease or the condition becomes stable.

The severity of events will be assessed on the following scale: mild, moderate, severe.

The relationship of AEs to the study medication will be assessed by the investigator.

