### Secondary outcomes

- Intubation in the delivery room (DR)
- Number of attempts taken to successfully intubate in the DR
- Chest compressions in the DR
- Adrenaline administration in the DR
- Rectal temperature on admission to the NICU
- NICU intubation
- Surfactant use before death or hospital discharge
  - Number of doses, including total dose
  - Intra-tracheal surfactant received post-intervention
  - Doses of post-intervention surfactant
- Respiratory distress syndrome
  - Clinical evidence of respiratory distress with radiological evidence (ground glass appearance on CXR)
- Incidence of pneumothorax
  - Incidence of pneumothorax on CXR
- Incidence of pulmonary haemorrhage
  - Clinical evidence of pulmonary haemorrhage
- Mechanical ventilation
- Days of mechanical ventilation
- Use of postnatal corticosteroids for ventilator dependence
- Days of duration of respiratory support (endotracheal ventilation, high-frequency oscillatory ventilation, CPAP, heated humidified high-flow nasal cannula  $O_2$ , low flow nasal cannula  $O_2$ )
- Bronchopulmonary dysplasia (BPD) – supplemental  $O_2$  at 28 days of life
- Chronic lung disease of prematurity (CLD) – need for supplemental  $O_2$  at 36 weeks corrected gestational age (CGA) determined by physiological oxygen reduction test
- Medical treatment for a patent ductus arteriosus
  - Administration of ibuprofen or paracetamol for PDA

- Surgical treatment for a patent ductus arteriosus
- Proven necrotising enterocolitis ( $\geq$  Bell's stage 2)
- Incidence of Intraventricular haemorrhage (IVH) (any and severe: IVH grade  $\geq 3$ )
  - Evidence on surveillance cranial ultrasounds performed regularly in NICU as standard of care
- Incidence of cystic periventricular leukomalacia
  - Evidence on surveillance cranial ultrasounds performed regularly in NICU as standard of care
- Retinopathy of prematurity treated with laser photocoagulation or intravitreal injections
  - Evidence on surveillance ophthalmology review performed regularly in NICU as standard of care
- Death before hospital discharge
- Survival without BPD at hospital discharge
- Survival without CLD at hospital discharge
- Duration of hospitalisation
- Use of home oxygen therapy
  - Discharged home on oxygen therapy

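### The adverse event waiver covers all intracranial haemorrhage, but the secondary outcome given as its reason covers only intraventricular haemorrhage

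*Combined protocol and SAP*

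**What the plan says.** Protocol section 13.3 reproduces the adverse reactions in the product information, among them "Haemorrhage intracranial". It then sets a general exemption: "AEs that are directly related to the underlying condition of extreme prematurity do not need to be reported as an AE on this study". Five numbered items follow as examples. Item 2 is intracranial haemorrhage. It notes that some degree of such bleeding is found in at least 30% of this population, says "Regular reporting of these adverse events in the CRF is not required", and adds "All enrolled infants are being screened for intracranial haemorrhage; it is being recorded in the CRF and measured as a secondary outcome". After the list comes the converse rule: "Only AEs which are not directly associated to the underlying condition of extreme prematurity should be reported".

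The secondary outcomes in protocol section 10.3 contain one intracranial bleeding entry. It begins "Incidence of Intraventricular haemorrhage (IVH) (any and severe: IVH grade" and sets the severe cut-off at grade 3 or higher. Its data source is given as "Evidence on surveillance cranial ultrasounds performed regularly in NICU as standard of care". Protocol section 11.3.2 repeats the entry. SAP section 1.3 assigns it two variables, one for any IVH and one for severe IVH. The only other cranial ultrasound outcome is cystic periventricular leukomalacia, which is not defined as a bleed.

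Protocol section 13.4 narrows SAE reporting to events that result in death and to important medical events.

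**The concern.** A waiver of this kind is sound when the waived event is collected and compared elsewhere. Here the waiver uses the broad product-information term and the replacement outcome uses a narrower one. A cerebellar or extra-axial bleed, for example, comes within the words of item 2 but is not named in either IVH variable.

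The broad term matters because the product information is the reference safety document (protocol 13.2.4) and the trial uses the product by an unlicensed route, in some infants below the licensed gestational age (protocol section 18). The Data Safety Monitoring Board (DSMB) reviews adverse events by group (protocol 13.5), and the safety tables are built from reported adverse events (protocol 14.6, SAP 5.4). An event that sites need not report does not reach either by that path. If no endpoint stands in for it, a difference between arms in such bleeds is not set up to be seen.

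**Working it through.** No arithmetic applies, so the check is a comparison of texts.

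**Step 1: waived events against listed outcomes.** For each item in protocol 13.3, the reason given is set beside the outcome lists in protocol 10.3, protocol 11.3.2 and SAP 1.3.

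| Item | Event waived | Reason given | Matching outcome listed |
|---|---|---|---|
| 1 | Bradycardia, hypotension, hyperoxia, cyanosis, apnoea, desaturation | Frequent, mostly brief and not clinically significant | None claimed |
| 2 | Intracranial haemorrhage | Recorded and measured as a secondary outcome | IVH only (any; grade 3 or more) |
| 3 | Bronchopulmonary dysplasia | Same as item 2 | Bronchopulmonary dysplasia |
| 4 | Pneumothorax, pulmonary haemorrhage | Same as item 2 | Pneumothorax; pulmonary haemorrhage |
| 5 | Endotracheal intubation complication | Not relevant to the study route | None claimed |

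Three items rest on a secondary outcome. In items 3 and 4 each waived event has an outcome of the same name. Item 2 is the only one whose waived event is wider than its outcome.

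**Step 2: where a non-ventricular intracranial bleed goes under the current text.**

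- It is fatal: reportable as an SAE (protocol 13.4) and counted in deaths by arm (SAP 5.4).
- It is judged an important medical event: reportable as an SAE under 13.4. Section 13.4 does not say how it interacts with the 13.3 waiver.
- It is judged not directly associated with extreme prematurity: reportable as an AE under 13.3.
- None of these: no AE report is required, and neither outcome list nor any SAP variable names it.

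**Step 3: how many infants are in the last group.** The figure of at least 30% in item 2 is for any intracranial haemorrhage and is not divided by site. No document gives a rate for non-ventricular bleeds, or the share of them that would be fatal, serious or judged unrelated to prematurity. The number cannot be derived.

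**The case against.** The strongest reply is that item 2 uses the product-information term loosely and means IVH. It calls the event a secondary outcome, and IVH is the only bleed read from surveillance ultrasound. That is a plausible account of the intention. The text does not say it, however, and a site following the text would leave out more than IVH.

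A reader might infer that non-ventricular bleeds vanish from the trial altogether. The documents do not support that, for four reasons:

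- Fatal bleeds and important medical events stay within SAE reporting, and SAEs are tabulated by arm.
- The exemption is limited to events directly related to extreme prematurity, and it lifts regular reporting without forbidding a report.
- Item 2 says that the event is recorded in the CRF. The CRF is not among the documents, so a field for other bleeds cannot be ruled out, and protocol 14.9 promises that all collected data will be described.
- The documents do not define whether parenchymal bleeding is scored within severe IVH, so part of what looks uncovered may be covered.

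All four points stand and limit the consequence. They do not close the gap. Item 2 itself presents intracranial haemorrhage as an example of a prematurity-related event, so the second route depends on an investigator departing from that example in an open-label trial. A CRF field alone would also leave these bleeds without a named comparison by arm.

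It is also fair that no efficacy estimate and no stopping boundary depends on this point. Any IVH, severe IVH and death are all compared between arms.

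**Conclusion.** The mismatch is in the text. The part of item 2's reason that can be checked, measurement as a secondary outcome, is met for IVH and not for other intracranial bleeds. The consequence is confined to bleeds that are non-ventricular, attributed to prematurity and not reported as SAEs: these have no required AE report and no named endpoint or SAP variable by arm.

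This is a minor point about completeness of safety capture. It rests on reading item 2 as written and on the outcome lists as they stand. It does not depend on any assumed event rate, and the documents support none. They also do not show that an excess of such bleeds is expected, or that the trial could detect a difference if every one were captured.

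**What to change.** Reconcile protocol 13.3 item 2 with the outcome lists in one of two ways.

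1. Limit the waiver in item 2 to IVH and say that any other intracranial haemorrhage is reported as an AE in both arms, whether or not it is attributed to prematurity. The last clause is needed because the numbered items are only examples of the general exemption. SAP 5.4 describes non-serious events by term only above 5% frequency in an arm, so the term should also be kept in the by-arm table promised in protocol 14.6.
2. Add to the SAP a by-arm summary of other intracranial haemorrhage, any site, taken from the routine cranial ultrasound reports. This needs no new scans. It also remains possible after enrolment has ended, which matters because protocol version 2.1 notes that some sites had begun close-out.

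With either option, add a sentence stating that the 13.3 waiver does not override SAE reporting under 13.4, and state whether parenchymal bleeding counts within severe IVH.

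The cost is a line of protocol text and a few more AE reports, or one extra variable to abstract from existing scan reports.
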